**Fig. 2 Fig2:**
[figure not shown]
Enrollment, intervention, and assessment in the ELEMENT trial

The investigator’s research personnel are responsible for entering all criteria on randomize.net which will then generate the randomization sequence. The research personnel involved in the statistical analysis and patients, but not the endoscopists, are blinded to treatment allocation. To ensure the quality of the trial, unblinding will occur only in exceptional circumstances when knowledge of the treatment allocation is essential for the optimal management of the patient.

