#### ERCP

A duodenoscope is advanced orally to the papilla. The bile duct is then cannulated with a sphincterotome using the guidewire-assisted technique. A cholangiogram is then performed followed by insertion of a self-expanding metal biliary stent. The performance of a biliary sphincterotomy prior to stent insertion and the choice of stent size (10 × 40 mm, 10 × 60 mm, 10 × 80 mm) and stent type (partially covered, fully covered, or uncovered) are recorded and left to the discretion of the endoscopist.

The assigned procedure (EUS-BD or ERCP) will be aborted in case of technical failure including inability to reach the papilla or cannulation failure in case of ERCP and inability to obtain a safe window for LAMS insertion in EUS-BD. A medical effectiveness approach is adopted, allowing additional procedures deemed indicated by the treating team (ERCP, EUS-BD, percutaneous drainage, and/or surgery) following the initial procedure in both groups, which will be recorded.

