### Follow-up

All patients are followed until either the primary outcome, surgery, death, or a total of 1-year post stent insertion have been reached, whichever comes first. A medical effectiveness approach is adopted, allowing additional therapeutic approaches deemed indicated by the treating team following the initial procedure in both groups, and are recorded.

Follow-up will be conducted over the phone and at subsequent office visits. If the patient is unable to be reached, a letter will be sent to their residence requesting a call back to the research assistant. A chart review can be performed in the event a patient is not able to be reached within a 2-week window of the follow-up date. If follow-up information is unable to be obtained, the patient will be considered a loss to follow-up and their data will documented accordingly. Any patient who deviates from the protocol or withdraws their consent from the ELEMENT trial at any point will be considered a protocol deviation and will be withdrawn from the data monitoring.

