##### Primary endpoint

Rate of re-intervention: Based on RCT data and retrospective series using LAMS [6–8, 10–12], we estimate a re-intervention rate of 30% vs. 10% for the ERCP and EUS-BD groups, respectively up to a 1-year follow-up period. To achieve a statistical power of 80% with a two-sided type I error of 5%, a total of 124 patients (62 in each arm) is required. Taking into account a 5% dropout rate, a final sample of 130 patients (65 patients in each arm) is needed.

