### Analyses

An intention-to-treat analysis along with a secondary per-protocol analysis will be carried out. Descriptive statistics will assess the adequacy of patient characteristics and balancing of the randomization process. Inferential analysis will employ Student’s *t* test and Chi-square testing. Survival analysis using the Kaplan–Meier method will be used to assess stent patency time. A step-wise multivariate regression analysis will be undertaken to identify independent predictors of stent dysfunction and adverse events using a log-rank test. A *p* value of 0.05 or less will be considered statistically significant. All analyses will be performed using SAS version 9.4. No interim analysis is planned given the short accrual time, relative small sample size, and short follow-up period.

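### The Follow-up section withdraws protocol deviators from data monitoring, which conflicts with its own rule to follow all patients and with the planned intention-to-treat analysis

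*Protocol article*

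**What the plan says.** Three statements in the protocol article bear on this.

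- **Follow-up, opening sentence:** "All patients are followed until either the primary outcome, surgery, death, or a total of 1-year post stent insertion have been reached", whichever comes first. Deviation is not among these end points.
- **Follow-up, last sentence:** "Any patient who deviates from the protocol or withdraws their consent from the ELEMENT trial at any point will be considered a protocol deviation". The sentence goes on to say that such a patient "will be considered a protocol deviation and will be withdrawn from the data monitoring". It comes directly after the rule for patients who cannot be reached and are counted as lost to follow-up.
- **Analyses:** "An intention-to-treat analysis along with a secondary per-protocol analysis will be carried out".

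Two further statements set the context. Under Treatment protocol, ERCP: "The assigned procedure (EUS-BD or ERCP) will be aborted in case of technical failure". The same paragraph continues: "A medical effectiveness approach is adopted, allowing additional procedures deemed indicated by the treating team", and says these procedures are recorded. The blinding paragraph under Randomization states: "The research personnel involved in the statistical analysis and patients, but not the endoscopists, are blinded to treatment allocation".

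**The concern.** An intention-to-treat analysis of an event counted over one year needs outcomes from everyone randomised, whatever their adherence. A rule that stops data on deviators removes part of what that analysis needs. The more deviators there are, the less the intention-to-treat analysis differs from the secondary per-protocol one.

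The rule also gives two different situations the same consequence. A patient who withdraws consent may have asked that no more data be collected. A patient who has only deviated has made no such request, and the outcome can still be obtained.

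Deviations arise after randomisation, in a trial whose endoscopists know the allocation. If deviators' risk of stent dysfunction differs from that of other patients, and differently by arm, losing their outcomes would bias the comparison as well as reduce precision. An analysis plan could not repair this, because it cannot recover outcomes that sites did not collect.

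**Working it through.** **1. The passages side by side.** Take a patient who deviates on day 30 with no stent dysfunction so far.

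- Opening rule of Follow-up: follow on, up to one year after stent insertion.
- Last sentence of Follow-up: withdraw from data monitoring.
- Analyses: include in the allocated arm for intention-to-treat; exclusion is a matter for the per-protocol analysis.

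The first and third agree. The second conflicts with both if data monitoring means follow-up data. The article does not define the term, but its place in Follow-up, after the loss-to-follow-up rule and paired with consent withdrawal, favours that meaning.

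**2. The plan's own sample size.** Inputs from Sample size calculation, Primary endpoint: "we estimate a re-intervention rate of 30% vs. 10% for the ERCP and EUS-BD groups, respectively up to a 1-year follow-up period"; 80% power; two-sided 5%; 1:1 allocation.

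n per arm = [1.96·√(2·0.20·0.80) + 0.8416·√(0.30·0.70 + 0.10·0.90)]² / 0.20²
= (1.109 + 0.461)² / 0.04 = 61.6, so 62 per arm and 124 in total. This matches the plan.

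Dropout: 124 / 0.95 = 130.5. The plan states 130, a rounding difference of no consequence here. The allowance is 130 − 124 = 6 patients.

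**3. Power under larger losses.** The loss rates above 5% are assumptions, since the article gives no deviation rate. With k patients per arm analysed:

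power = Φ{[0.20·√k − 1.96·√0.32] / √0.30}

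- No loss, k = 65: 82.1%
- 5% loss (planned), k = 61.75: 80.1%
- 10% loss, k = 58.5: 77.9%
- 15% loss, k = 55.25: 75.5%
- 20% loss, k = 52: 72.9%

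**4. Few events in the EUS arm.** Expected events: 65 × 0.10 = 6.5. As an illustration, start from 7/65 = 10.8%. Losing one patient with an event gives 6/64 = 9.4%; losing two gives 5/63 = 7.9%. That the lost patients had events is an assumption made to show sensitivity.

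**5. Effect of informative loss.** All inputs here are assumed. Suppose the true rate is 20% in both arms, and a fraction f of one arm only is removed, with event rate r among those removed. The rate left in that arm is (0.20 − f·r)/(1 − f). Type I error is from a normal approximation with 65 and 65(1 − f) patients.

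- f = 5%, r = 20%: no false difference, type I error 5%
- f = 5%, r = 40%: 1.1 points, about 5.3%
- f = 5%, r = 60%: (0.20 − 0.03)/0.95 = 17.9%, 2.1 points, about 6.1%
- f = 10%, r = 40%: 2.2 points, about 6.1%
- f = 10%, r = 60%: (0.20 − 0.06)/0.90 = 15.6%, 4.4 points, about 9.9%

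If those removed have the same risk as the rest, there is no bias. Bias needs both one-sided loss and a markedly different risk.

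**The case against.** The strongest reply is that one loosely worded sentence stands against two clear ones. It speaks of data monitoring, not data collection, and Data collection is a separate section. Trial management uses monitoring for regular oversight of the database. The article nowhere says that deviators' data are discarded or that they are left out of the analysis. Planning a separate per-protocol analysis suggests that they stay in the intention-to-treat one. This shows that the intended meaning may be harmless. It does not remove the conflict, because sites act on the sentence as written.

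Several stronger readings are tempting, but the article does not support them.

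- **That technical failures are deviators.** A reader might apply the 95% technical success assumed for ERCP and count 65 × 0.05 = 3.25 deviators per arm, enough to use up the dropout allowance. But aborting after technical failure and then using another procedure is provided for in the protocol, so rescue and crossover are not in themselves deviations. Stent choices left to the endoscopist are not deviations either, and patients who cannot be reached have their own pathway.
- **That intention-to-treat becomes impossible or turns into an as-treated analysis.** Patients could still be analysed as randomised with data to last contact, and nothing reassigns them by treatment received. What is lost is their later outcomes.
- **That technical success is biased.** It is settled at the initial procedure (Table 3, item 1), so stopping later follow-up does not remove it.
- **That deviations are known to be tied to treatment.** The article gives neither reasons nor rates. Unblinded endoscopists and arm-specific reasons for aborting make informative loss possible, no more.

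Also, a patient whose dysfunction came before the deviation has already reached the endpoint, so only later events are at risk.

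**Conclusion.** The concern holds as a contradiction in the current text. The last sentence of Follow-up, on its natural reading, ends outcome capture for deviators, against both that section's opening rule and the Analyses section. It should be corrected, because data not collected under it may not be recoverable.

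The size is unknown. On assumed total losses of 10% to 20%, power falls from about 80% to between 78% and 73%, and one or two lost events would shift the EUS-arm estimate by about 1 to 3 percentage points. Bias is possible but not shown. It would depend on how many patients sites class as deviators, on whether their risk differs, and on whether this is unequal between arms. The stated sample size reproduces and is not in question.

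**What to change.** Replace the last sentence of Follow-up with wording to this effect: protocol deviations are recorded; the patient stays in follow-up to the planned end and in the intention-to-treat analysis in the allocated arm; deviators are excluded only from the secondary per-protocol set; only withdrawal of consent to further data collection ends follow-up, and data up to that date are kept as the consent allows. It would help to add that the additional procedures permitted under Treatment protocol are not, in themselves, deviations.

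The sample size stays at 130. The cost is a one-sentence amendment, a note to sites and continued follow-up of a few patients who have already consented.

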### Statistical aspect

#### Sample size calculation

The sample size calculation is based on the primary endpoint of rate of re-intervention and we are assessing for superiority. We also include a non-inferiority sample size calculation for the secondary endpoint of technical success to ascertain the adequacy of statistical powering for other outcomes (Fig. 3).

**Fig. 3 Fig3:**
[figure not shown]
Flowchart ELEMENT trial

##### Primary endpoint

Rate of re-intervention: Based on RCT data and retrospective series using LAMS [6–8, 10–12], we estimate a re-intervention rate of 30% vs. 10% for the ERCP and EUS-BD groups, respectively up to a 1-year follow-up period. To achieve a statistical power of 80% with a two-sided type I error of 5%, a total of 124 patients (62 in each arm) is required. Taking into account a 5% dropout rate, a final sample of 130 patients (65 patients in each arm) is needed.

##### Secondary endpoints

Technical success: we estimate a technical success of 95% in the ERCP cohort [6–8]. A non-inferiority margin of 10% is implemented. To achieve a statistical power of 80% with a one-sided type I error of 5%, a total of 118 patients (59 in each arm) is required. Taking into account a 5% dropout rate, 124 patients (62 patients in each arm) are needed. Therefore, with a sample size of 130 patients, we are adequately powered for both the primary and main secondary endpoints.

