### Endpoints

The primary endpoint is the rate of stent dysfunction (including both migration and occlusion) needing endoscopic or radiological re-intervention (Table 2). Patients who reach the primary endpoint are considered to have completed the study once hospitalization time for stent dysfunction and delays in chemotherapy treatment have been captured. Patients who do not reach the primary outcome are followed until surgery, death, or up to 1-year post stent insertion.

**Table 2 Tab2:** Criteria for primary endpoint of stent dysfunction

Meeting one or more of the following criteria:	
□ Suspected cholangitis [13]	
□ Definite cholangitis [13]	
□ 50% increase in bilirubin from the lowest level post index procedure	
□ 20% increase in bilirubin from the lowest level post index procedure AND evidence of obstruction on imaging (US/CT/MRI)	
AND:	
□ Endoscopic or radiological re-intervention confirming stent blockage or migration needing stent cleaning, stent change, and/or additional stent insertion

**Table 3 Tab3:** Secondary endpoints

1. Technical success defined as successful insertion of a transpapillary stent or choledochoduodenostomy stent at the initial procedure at time of randomization [6–8]	
2. Clinical success defined as 50% decrease in bilirubin < 2 weeks post-stent insertion or less than 25% of pre-procedure bilirubin level within 4 weeks post stent insertion [6]	
3. Stent patency defined as mean time to stent obstruction or migration (patient will be censored at last-follow-up or death)	
4. Proportion of patients with interruptions in chemotherapy treatment due to recurrent stent dysfunction	
5. Early adverse events (within 14 days of index procedure) as defined per the ASGE lexicon for endoscopic adverse events [18], including post-procedural pancreatitis, bleeding, intestinal perforation, and cholangitis	
6. Delayed adverse events (greater than 14 days of index procedure until last follow-up or death)	
7. Cost-effectiveness analysis	
Additional outcomes	
1. Median number of days in delayed chemotherapy treatment if interrupted	
2. Procedure time defined as from insertion of the endoscope to endoscope withdrawal1	
3. Fluoroscopy time	
4. Rate of hospitalization and length of stay	
5. Mortality	

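### Technical success is sized as a non-inferiority comparison with a 10-point margin, but the only test stated for proportions is a chi-square, which tests equality and never uses the margin

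*Protocol article*

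**What the plan says.** In the Protocol article, under Sample size calculation, Secondary endpoints, technical success gets its own calculation. The control rate is given: "we estimate a technical success of 95% in the ERCP cohort". The margin is given: "A non-inferiority margin of 10% is implemented". The level is a one-sided 5% with 80% power, and the result is "a total of 118 patients (59 in each arm) is required". After dropout it becomes 62 per arm. Because the trial recruits 130, the section concludes that "we are adequately powered for both the primary and main secondary endpoints".

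The Design and objectives section makes comparable technical success part of the trial hypothesis.

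The Analyses section covers testing in one sentence for the whole trial: "Inferential analysis will employ Student’s *t* test and Chi-square testing". A p value of 0.05 or less counts as significant. Intention-to-treat and secondary per-protocol analyses are planned. The margin is not mentioned there, and no confidence limit or non-inferiority decision rule appears anywhere in the document.

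**The concern.** A non-inferiority design tests the null hypothesis that EUS-guided drainage is worse by 10 points or more, and it succeeds by rejecting that hypothesis. A chi-square tests the null hypothesis of no difference. Failing to reject it, with 62 to 65 patients per arm, says little about whether a 10-point loss has been ruled out.

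This is more than missing detail. The protocol names a test, and that test does not fit the hypothesis for which it claims power. The 80% figure describes a comparison with the margin and says nothing about the chi-square. At stake is one of the trial's supporting conclusions: that a first-intent EUS approach gives up little in technical success.

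**Working it through.** **Inputs.** ERCP success 95%, margin 10 points, one-sided 5%, power 80%, 59 per arm before and 62 after dropout (Secondary endpoints); 65 per arm recruited (Primary endpoint). Assumption: EUS success is also 95% under the alternative. The protocol gives no EUS rate, but equal rates reproduce its figure.

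**1. The protocol's own figure.**
n per arm = 2·p(1−p)·(z₀.₉₅ + z₀.₈₀)² / Δ² = 2 × 0.95 × 0.05 × (1.645 + 0.842)² / 0.10² = 58.7, so 59 per arm and 118 in total. This matches. Dropout: 118 × 1.05 = 123.9, so 124, as stated. (Dividing by 0.95 gives 125, which is immaterial with 130 recruited.)
The same formula gives power at one-sided 5% of Φ(0.10/√(0.095/n) − 1.645): 82% at n = 62 and 83% at n = 65.

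**2. The two rules.**
- Chi-square: non-significant if |p_EUS − p_ERCP| / √(2·p̄(1−p̄)/n) < 1.96. The margin does not enter.
- Margin rule (Wald): non-inferior if (p_EUS − p_ERCP) − 1.645·√(p_EUS(1−p_EUS)/n + p_ERCP(1−p_ERCP)/n) > −0.10.

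**3. How often each rule passes an EUS arm that is worse by the full margin.** True rates are 95% and 85%. Binomial probabilities are summed over all pairs of outcomes.

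| Per arm | Chi-square non-significant | Same, continuity-corrected or Fisher | Wald lower limit above −10 points |
|---|---|---|---|
| 59 | 54.6% | 68.2% | 6.5% |
| 62 | 52.7% | 65.7% | 6.0% |
| 65 | 50.7% | 63.3% | 6.7% |

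The normal approximation gives 54% and 52% for the first column at 62 and 65 per arm. At 65 per arm, 50.7 − 6.7 = 44.0% of such trials would show no significant difference and yet fail the margin.

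**4. One possible result.** 56/65 EUS against 62/65 ERCP is 86.2% against 95.4%, a difference of −9.2 points. The pooled rate is 118/130 = 0.908, so z = 0.0923 / √(2 × 0.908 × 0.092 / 65) = 1.82 and p = 0.069, not significant. The Wald one-sided 95% lower limit is −9.2 − 1.645 × 5.01 = −17.5 points, well past the margin.

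**5. The margin rule when the arms are truly equal at 95%.** The same enumeration gives a pass in 79% (59 per arm), 82% (62) and 84% (65). The stated power therefore holds for a Wald limit at the stated level.

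**6. Few failures.** At 95% success, 65 × 0.05 = 3.25 failures are expected per arm, so the choice of interval matters. I repeated steps 3 and 5 with a score limit (variance from the rates fitted under a difference of −10 points). At 62 and 65 per arm it passes an arm worse by the full margin in 4.5% and 4.7% of trials, and truly equal arms in 72% and 76%.

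**The case against.** The strongest objection is that the Analyses sentence is generic. It lists families of tests for the whole trial, does not assign the chi-square to technical success, and does not say that non-significance means comparable. An analysis plan that is not shown may hold the margin-based test. This limits the point: the 51 to 53% is the consequence of one natural reading and not a rule that the protocol states. It does not remove the mismatch, because an analysis plan would have to go beyond the protocol's stated tests to match the protocol's own design.

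Two stronger readings are tempting, and the document supports neither.

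- *That the power claim is false because one-sided 2.5% should apply.* At that level 75 per arm would be needed. But the protocol states one-sided 5% openly, its number reproduces at that level, and its power claim holds there. The level is a declared choice, not an error.
- *That the endpoint credits the other arm's stent.* Table 3 reads "Technical success defined as successful insertion of a transpapillary stent or choledochoduodenostomy stent at the initial procedure", which could in isolation cover either stent in either arm. But the Treatment protocol lists arm-specific technical failures of the assigned procedure and treats other drainage as additional procedures that follow it. Read together, these largely tie success to the assigned procedure.

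It is also fair that technical success is secondary. The trial is sized on the superiority comparison, which is unaffected.

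**Conclusion.** The point holds as a mismatch between design and stated analysis. The sample size for technical success is correct for a non-inferiority comparison at one-sided 5%, but the only test stated for proportions cannot deliver a non-inferiority conclusion.

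If a non-significant chi-square were taken as showing comparability, an EUS arm worse by the full 10 points would pass in about 51 to 53% of trials at 65 to 62 per arm, against about 6 to 7% for a Wald limit compared with the margin. This rests on true rates of 85% and 95%, on an uncorrected chi-square (a corrected or exact test gives 63 to 66%), and on that reading of non-significance, which a reader would infer and the protocol does not state. It should be fixed before analysis. It does not threaten the primary result.

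**What to change.** In the Analyses section, state that technical success is analysed as the risk difference, EUS minus ERCP, with a confidence interval suited to few failures, such as a score interval. State that non-inferiority is concluded only if the one-sided 95% lower limit (the lower end of the two-sided 90% interval) is above −10 points. That is the level the sample-size section already sets.

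Apply the rule in the intention-to-treat set, with the per-protocol analysis as support. Say that the per-protocol set does not drop patients because their assigned procedure failed technically; otherwise the endpoint's own failures are removed and both arms drift towards 100%.

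The cost is wording. No patients are added, and the power stated from the protocol's formula can stand. Name the interval in advance, because it involves a trade-off: at 62 to 65 per arm the Wald limit has about 82 to 84% power with 6 to 7% error at the margin, while the score limit keeps the error below 5% with about 72 to 76% power.
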